### Data collection

After their informed consent to participate, GDPs will be invited to first complete a questionnaire to collect personal and practice characteristics, as well as aspects of attitude and compliance. Individual assessment of electronic patient records with regard to the outcome measures, combined with a special registration form (to be applied individually in daily practice), will be used during the evaluation period.

Baseline information will be collected before randomisation of groups, as well as at the end of the trial after seven to nine months. Each GDP will be instructed to complete at least 20 forms per registration period. As each peer group consists of at least eight participants, and each arm will consist of three groups, this will result in a minimum of 480 registrations per trial arm. Finally, questionnaires will be collected from GDPs, dentist's assistants and co-workers to assess acceptance and applicability.

### Sample size

The primary outcome measures in this study are collected from individual patients who are clustered within GDPs. GDPs are clustered within (existing) IQual groups which have been randomised to one of the two arms of the trial. The power calculation assumes that the primary outcomes are dichotomous measures, although some outcomes might be treated as continuous measures as well. On the basis of previous research and experience with IQual groups, we expect a relatively high clustering of scores within GDPs, for instance, the intra-cluster coefficient (ICC) for recall interval assignment was 0.29 [23], and a low clustering of scores within IQUAL groups (changing professional behaviour is largely determined by other factors). We use the ICC for clustering in IQual groups, because this was the unit of randomisation. We aim for a 20% change on primary outcomes (e.g. 20 to 40% patients receive individualised recall intervals). Assuming *a power of *80%, alpha = 0.05 and an effect size of 20% for both interventions and an estimated ICC of 0.03 based on previous estimates [21,22], the (Aberdeen) power calculation [24] revealed that six IQual groups (60 GDPs) should comprise 150 registrations (patients) per group, resulting in at least 450 registrations in each trial arm.

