## Discussion

Little evidence was available on the estimates of the likely size of dental primary care ICCs, and which prognostic factors influenced their magnitude. Based on research in this field, we assumed a substantial variation in primary dental care between fairly autonomous GDPs [25-28]. Data extracted from primary health care suggested that ICCs for patient outcomes in primary care were generally less than 0.05 [21,22]. In reviews of this protocol, questions were raised about the power calculation. In particular, the expected effect size was seen as large, and the applied ICC as low. This would imply that the power calculation is too optimistic, and that the study might be underpowered to detect meaningful change in professional behaviour.

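### The 80% power for six IQual groups makes no allowance for three randomised groups per arm; on the plan's own inputs a post-intervention comparison on 4 degrees of freedom has about 58%

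*Protocol article*

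**What the plan says.** The IQual group is the unit of randomisation (Randomisation), and each arm has three groups (Data collection). The Sample size section sets these inputs:

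- Outcome: "The power calculation assumes that the primary outcomes are dichotomous measures".
- Effect: "We aim for a 20% change on primary outcomes (e.g. 20 to 40% patients receive individualised recall intervals".
- Error rates: power of "80%, alpha = 0.05 and an effect size of 20% for both interventions".
- Clustering: "an estimated ICC of 0.03 based on previous estimates". The same section reports that "the intra-cluster coefficient (ICC) for recall interval assignment was 0.29" at GDP level and expects clustering within IQual groups to be low. It then explains its choice: "We use the ICC for clustering in IQual groups, because this was the unit of randomisation".

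The result is that "six IQual groups (60 GDPs) should comprise 150 registrations (patients) per group, resulting in at least 450 registrations in each trial arm".

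The Statistical analysis section defines the intervention effect as the interaction of allocation and measurement time in random-effects regression. The Discussion reports that the effect size was seen as large and the ICC as low, and adds: "This would imply that the power calculation is too optimistic, and that the study might be underpowered to detect meaningful change". It offers no other power figure.

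**The concern.** Randomising six groups fixes how much information there is on the between-group error: six group results less two arm means leave 4 degrees of freedom. The two-sided 5% critical value is then 2.776, not 1.96. A calculation with normal quantiles and a design effect inflates the variance for clustering but treats that variance as known. With dozens of clusters this matters little; with six it matters a great deal.

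A second question is what 0.03 stands for. The section quotes a GDP-level ICC about ten times larger and enters only the group-level value. Choosing the level of randomisation does not remove the variance at the level below, unless the group-level value is meant to include it.

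At stake is the only power figure in the article. A reader who accepts both the 20-point effect and the ICC of 0.03 would still believe 80%.

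**Working it through.** **Inputs.** From Sample size: 20% vs 40%, alpha 0.05 (two-sided assumed), ICC 0.03, GDP ICC 0.29, six groups of 150. From these, 60 GDPs / 6 = 10 GDPs per group, and 150 / 10 = 15 registrations per GDP. From Data collection: three groups per arm.

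**1. The stated figure.**
- Independent patients per arm, pooled normal formula: [1.96·√(2·0.3·0.7) + 0.842·√(0.16 + 0.24)]² / 0.2² = 81.2, so 82.
- Design effect: 1 + (150 − 1)·0.03 = 5.47.
- 82 × 5.47 = 448.5, hence 450 per arm; power is 80.5%.
- The unpooled formula gives 429 and the continuity-corrected one 498, so neither matches. The 450 is therefore a normal-quantile calculation with one ICC.

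**2. Same inputs, 4 degrees of freedom.**
- Effective n per arm: 450 / 5.47 = 82.3.
- Standard error: √(0.40 / 82.3) = 0.0697; noncentrality 0.20 / 0.0697 = 2.87.
- Noncentral t, 4 df, critical value 2.776: power 58%. With pooled variance (0.42) it is 56%. A simulated t-test on group proportions (40,000 runs) also gives 58%.
- At the Data collection minimum of 8 GDPs × 20 forms (480 per arm) it is 59%.
- Difference detectable with 80% power from a base of 20%: about 26.5 points. Check: √((0.16 + 0.465·0.535) / 82.3) = 0.0705, and 0.265 / 0.0705 = 3.76, the noncentrality that 80% requires on 4 df.

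**3. GDP clustering, ROE outcome only.**
- *Additive reading:* 0.03 is the correlation between patients of different GDPs in one group, and 0.29 that between patients of the same GDP. Design effect 1 + 14·0.29 + 9·15·0.03 = 9.11; effective n 450 / 9.11 = 49.4; standard error √(0.40 / 49.4) = 0.0900; noncentrality 2.22; power 40% (38% pooled; simulation 40%). The detectable difference is about 34 points. With 8 GDPs × 20 forms, power is 37%.
- *Averaged reading:* 0.03 is the mean correlation over all pairs in a group. GDP clustering alone contributes 14·0.29 / 149 = 0.027, so 0.03 absorbs it if patients of different GDPs correlate at only (5.47 − 1 − 14·0.29) / 135 = 0.003. The design effect stays 5.47 and power stays near 58%.

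**4. Planned allocation-by-time analysis.** The article gives no baseline-to-follow-up correlation, so *r* is assumed, equal for group and GDP effects, with different patients in each period. Variance of a group's change: 2·0.20·[g(1 − r) + d(1 − r)/10 + e/150], where g, d and e are the group, GDP and patient shares; standard error √(2·variance / 3); t on 4 df.
- Additive (g 0.03, d 0.26, e 0.71). At r = 0.5 the bracket is 0.0327, the standard error 0.0934 and power 37%. At r = 0.9 they are 0.0103, 0.0525 and 81%.
- Averaged (g 0.003, d 0.287, e 0.71). At r = 0.5 the bracket is 0.0206, the standard error 0.0741 and power 54%. At r = 0.9 they are 0.0079, 0.0459 and about 90%.
- Using 0.16 for every cell except 0.24 for intervention at follow-up, in place of a common 0.20, raises these to 40% and 83% (additive) and 57% and 91% (averaged).

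In round terms: about 37–82% on the additive reading and about 57–91% on the averaged one.

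**The case against.** **The arithmetic is not wrong.** The 450 and the 80% follow from the inputs. This stands: the fault is in the method, which takes normal quantiles for six clusters.

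**The planned analysis is not a post-intervention comparison.** This also stands, and it limits the claim. A reader might infer that the design delivers 40–58%. The article does not support that, because its analysis uses baseline data from the same GDPs and high enough correlations would lift power to 80% or more. However, the Sample size section claims no gain from baseline, and its figure matches a post-intervention comparison.

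**The GDP ICC may already be inside the 0.03.** A reader might infer that 0.29 was wrongly left out. The text does not settle this. An ICC at the level of the randomised unit can be read as an average that includes GDP clustering, and the section does expect low clustering in IQual groups. The 0.29 is also quoted for recall intervals only, so the 40% cannot be carried to the MIM outcome.

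**The Discussion already concedes low power.** In part. It names effect size and ICC, not the number of groups, and leaves the 80% standing. It does rule out the further inference that a null result would be presented as evidence of no effect; nothing in the article says so.

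**A random-effects model could show more power.** Only if the effect were tested against a normal reference. With 4 df of between-group information, the two-sided error would be about 2·P(t₄ > 1.96) = 12% rather than 5%. The article does not say which reference it will use.

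**Conclusion.** The concern holds in this form. The stated 80% is not the power of the comparison it was computed for. With three randomised groups per arm it is about 58% (56% with pooled variance). That loss needs no outside figure and no view on GDP clustering, and it applies to both primary comparisons, since both share the effect size and ICC.

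The rest is conditional. Power near 40% applies to the ROE outcome only, and only if 0.29 comes on top of 0.03. Power of the planned analysis rests on correlations the article does not give: for assumed values of 0.5 to 0.9, about 37–82% (additive) or about 57–91% (averaged). No single figure can be assigned to the design until the meaning of 0.03 and those correlations are stated. All figures assume a two-sided test, equal group sizes and 10 GDPs × 15 registrations unless noted.

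**What to change.** In Sample size, replace the 80% statement with power computed on a t reference with 4 degrees of freedom, and:

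- say whether 0.03 is the correlation between patients of different GDPs or the average over all pairs in a group, and whether GDP clustering is included;
- give about 58% for both comparisons, and about 40% for ROE if the additive reading is meant;
- give the range for the allocation-by-time analysis under stated, assumed correlations;
- give the matching detectable difference (for the post-intervention comparison, about 26.5 points, or about 34 for ROE on the additive reading).

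In Statistical analysis, state that the intervention effect is tested with group-level degrees of freedom and reported with its confidence interval. In the Discussion, name the number of groups as a cause of limited power.

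The cost is rewording and a less favourable stated power. No groups or registrations are added.

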### Statistical analysis

The primary analysis will be performed on an intention-to-treat-analysis. Secondly, measures will be constructed in particular algorithms to define the appropriateness in variables. Thirdly, the impact on each of the primary and secondary outcomes will be estimated separately, using random effects regression models (linear or logistic) to take into account the clustering of data. These basic models include group allocation (intervention, control), measurement timing (baseline, post-intervention), and interaction of group allocation and measurement timing (=intervention effect). Fourthly, prognostic factors for the outcome (which may be confounders) will be added to the models, like patients' recall interval preferences, which varies from those assigned by GDPs, as well as the preferences regarding the prescription of radiographs by patients/GDPs. In addition, this also accounts for GDPs and patients' preferences regarding removal versus retention of asymptomatic impacted third molars. Fifthly, a limited number of subgroup analyses will be performed, including an analysis of effectiveness in participants which performed all activities as planned, i.e., education session, online training program, and helpdesk (= efficacy analysis).

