### Randomisation

After their commitment to participate, 60 GDPs nested in six IQual groups were randomly assigned (using SPSS) as groups to the ROE or MIM arm by an independent secretary not familiar with the groups. The unit of randomisation was the IQUAL group.

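### With only six randomised groups, the planned random-effects test of the allocation-by-timing interaction could exceed 5% type I error unless by-period cluster variation and a small-sample test are specified

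*Protocol article*

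**What the plan says.** The Randomisation section states that "60 GDPs nested in six IQual groups were randomly assigned (using SPSS) as groups to the ROE or MIM arm" and that "The unit of randomisation was the IQUAL group". Under Data collection, "each arm will consist of three groups", with at least eight GDPs per group and at least 20 forms per GDP in each registration period.

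The Statistical analysis section estimates the effect on each primary and secondary outcome "using random effects regression models (linear or logistic) to take into account the clustering of data". The terms it lists for the basic models are allocation, measurement timing and the "interaction of group allocation and measurement timing (=intervention effect"). It does not say which levels carry random effects, whether those effects may differ between baseline and follow-up, or which reference distribution is used.

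The Sample size section recognises that patients are nested in GDPs and GDPs in IQual groups. It assumes a group-level ICC of 0.03, reports an ICC of 0.29 within GDPs for recall interval assignment, and plans for "80%, alpha = 0.05 and an effect size of 20% for both interventions", for example "20 to 40% patients receive individualised recall intervals". The result is 150 registrations per group and 450 per arm. The Discussion concedes that the effect size may be large and the ICC low. It does not mention test size with six clusters.

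**The concern.** There are two separate issues.

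**Error term.** A random intercept for a group or GDP takes the same value at baseline and follow-up. In a linear model with balanced data it therefore cancels from a before-after contrast. If the model has intercepts only, the interaction is judged against patient-level error. The error that matters in a group-randomised trial is how much groups, and the GDPs within them, differ in their change over time. Such differences are plausible here: each group has its own meeting, GDPs are described as fairly autonomous, and months separate the two registration periods.

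**Reference distribution.** Even with the right standard error, three groups per arm give 4 degrees of freedom. Comparing the estimate with a normal distribution treats a variance estimated from six units as if it were known.

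In either case intervals could be too narrow, and one of the programmes could be declared effective by chance more often than the nominal 5%. Restating the power does not remove this, because it concerns the validity of the test.

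**Working it through.** **Inputs from the article**
- 6 groups, 3 per arm (Randomisation; Data collection).
- At least 8 GDPs per group and 20 forms per GDP and period, so 8 × 20 = 160 patients per group and period (Data collection).
- Group ICC 0.03, GDP ICC 0.29, 20% versus 40%, alpha 0.05, power 80%, 150 per group, 450 per arm (Sample size).

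**Assumed, because the article does not give it:** the correlation c between a cluster's effect at baseline and at follow-up, taken from 1 (perfectly stable) to 0.

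**Step 1: reproduce the plan's figure.** The two-sided normal-theory size for 20% versus 40% is
[1.96·√(2·0.3·0.7) + 0.842·√(0.16 + 0.24)]² / 0.2² = 81.2, so 82 per arm.
The design effect is 1 + 149 × 0.03 = 5.47, and 82 × 5.47 = 448.5, or 449 against the stated 450. The figure is reproduced, and it contains no allowance for 4 df.

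**Step 2: z test with a correct standard error.** The df are 6 − 2 = 4, and P(|t₄| > 1.96) = 12.2%. This is the rate for a model that does carry group-by-period variation, without restricting that variance to be non-negative. If the variance is truncated at zero, simulation gives about 4% to 12%.

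**Step 3: random intercepts only, z test.** The variance of the interaction is understated by a factor F, and the type I error is 2·[1 − Φ(1.96/√F)].

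(a) Group ICC 0.03 alone: F = 1 + 160 × 0.03 × (1 − c)/0.97.

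(b) Total GDP ICC 0.29, with group share 0.03, GDP share 0.26 and residual 0.71, both shares having the same c: F = 1 + 160 × (1 − c) × (0.03 + 0.26/8)/0.71.

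| c | F (a) | type I (a) | F (b) | type I (b) |
|---|---|---|---|---|
| 1 | 1.00 | 5% | 1.00 | 5% |
| 0.9 | 1.49 | 11% | 2.41 | 21% |
| 0.7 | 2.48 | 21% | 5.23 | 39% |
| 0.5 | 3.47 | 29% | 8.04 | 49% |

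For (a) at c = 0, F = 5.95 and the rate is 42%.

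**Step 4: check by simulation.**
- A binary outcome at 20% prevalence with no effect (4,000 trials per setting, 8 × 20 per group and period) gave 11%, 22% and 30% for (a), and 20%, 38% and 48% for (b), at c = 0.9, 0.7 and 0.5.
- A linear model (40,000 trials per setting) with the same layout and group ICC 0.03 alone gave 5.0%, 11.1%, 29.3% and 42.3% at c = 1, 0.9, 0.5 and 0.
- A t reference on 4 df (critical value 2.776) held 4.4% to 5.2% in the binary simulation and 4.7% to 5.2% in the linear one.

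**Step 5: cost in power on the plan's own inputs** (post-intervention comparison, as in the sample-size calculation). The effective size is 450/5.47 = 82.3 per arm. The normal reference gives 80.5%. With 4 df, the non-centrality is 0.2/√(0.40/82.3) = 2.87 and the power is 58%.

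**The case against.** The strongest reply is that the article does not state the faulty analysis. The listed terms are the fixed part of the model. The text does not say intercepts only, does not exclude by-period random effects and names no z test. The full protocol or an analysis plan may settle these points, and the Sample size section shows that the authors understood the nesting and the unit of randomisation. Small-sample degrees of freedom are a standard option for linear mixed models. All of this stands, and it makes the point conditional.

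A reader might draw four stronger conclusions that the documents do not support:
- **That the plan commits to an invalid test.** It leaves the choice open.
- **That 12% is the minimum error rate.** That figure belongs to a model that includes by-period variation and uses z. An intercept-only model holds about 5% when cluster effects are stable.
- **That rates above 40% are to be expected.** They need substantial period-specific variation, and the article gives no figure for it.
- **That every outcome is affected to this extent.** The calculations cover patient-level outcomes. The GDP questionnaires, the patient interviews and the practice-level third-molar proportion over five years were not examined.

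The reply does not remove the point. The section goes as far as fixing the model class, its listed terms and the effect tested. The usual fit of that model does not protect this interaction with six clusters, and the one inferential calculation shown uses normal theory.

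**Conclusion.** The point holds in conditional form. Three groups per arm leave 4 between-group degrees of freedom, and the analysis text secures neither the right error term nor a suitable reference distribution. Depending on how it is carried out, type I error could lie anywhere from about 5% to over 40%. The lower end applies to intercept-only models with perfectly stable cluster effects. The upper end requires either group effects that are almost wholly period-specific (42% with ICC 0.03 alone) or marked instability at GDP level as well (49% at correlation 0.5). The 12.2% for a z test on 4 df is exact. The intercept-only figures rest on the assumed over-time correlation, a balanced layout and the article's ICCs.

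**What to change.** For the patient-level outcomes, state one of the following:

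1. A mixed model in which both IQual-group and GDP effects may vary by period, with the interaction tested against a t distribution with about 4 df.
2. A t test on 4 df comparing the six group-level changes between arms. This is the simpler choice for logistic outcomes, or when the group-by-period variance is estimated at zero and a model-based df method may not return about 4 df.

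Base the 95% intervals on the same distribution as the test.

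The change takes a few lines of text and needs no new data. The cost is wider intervals and a loss of power, from about 80% to about 58% on the protocol's own inputs. That figure should be stated next to the sample-size calculation, because the Discussion's existing caveat covers only the effect size and the ICC.

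### The 80% power is calculated for a single-time comparison, but the planned test is the allocation-by-time interaction, whose power depends on an over-time correlation the protocol does not give

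*Protocol article*

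**What the plan says.** The Sample size section sets the target: "We aim for a 20% change on primary outcomes (e.g. 20 to 40% patients receive individualised recall intervals"). It assumes "alpha = 0.05 and an effect size of 20% for both interventions" together with "an estimated ICC of 0.03 based on previous estimates", and concludes that "six IQual groups (60 GDPs) should comprise 150 registrations (patients) per group, resulting in at least 450 registrations in each trial arm". Neither a baseline measurement nor a correlation between periods enters the calculation.

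The Statistical analysis section describes random-effects models with allocation, measurement time and their product as fixed terms. It names the effect of interest as the "interaction of group allocation and measurement timing (=intervention effect"). Because allocation is also a main effect, each arm has its own baseline level.

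On timing, the Data collection section states: "Baseline information will be collected before randomisation of groups". It asks each general dental practitioner (GDP) for at least 20 forms in each registration period. The Analysis section under Economic evaluation is looser: it lets pre-test measurement run into the intervention period where data are sampled retrospectively.

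**The concern.** A sample size supports a trial only if it is worked out for the contrast that will be tested. An interaction between arm and period is the difference between two before-after changes. It carries the sampling error of both periods, reduced by the correlation between them. If that correlation is low, the interaction is less precise than a comparison of the arms after the intervention. If it is high, the interaction is more precise. The protocol gives the correlation nowhere, so a reader cannot tell which case applies or whether 80% is met. With three groups per arm there is little margin, and a null result could be read as coming from an 80% power trial when the real figure might be well below that.

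**Working it through.** **Inputs.** Rates 20% and 40%, alpha 0.05 (taken as two-sided), ICC 0.03 at IQual-group level, 150 registrations per group and 450 per arm (Sample size); three groups per arm (Data collection). The count is per period: 20 forms x 8 GDPs x 3 groups = 480 per arm in each registration period. Two inputs are assumptions: the autocorrelation of the group effect between periods (CAC), which is not given and is varied from 0 to 1, and different patients in each period.

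**1. The plan's own figure.** Two proportions, pooled variance, no continuity correction: n = [1.96 x sqrt(2 x 0.3 x 0.7) + 0.8416 x sqrt(0.16 + 0.24)]^2 / 0.2^2 = 81.2, so 82 per arm. Design effect = 1 + 149 x 0.03 = 5.47. Then 82 x 5.47 = 448.5, against 450 stated. The continuity-corrected version gives 91 x 5.47 = 498 and the unpooled version 429. The stated figure is therefore a single-time comparison multiplied by a design effect.

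**2. Single-time benchmark on the scale used below.** Effective size per arm = 450 / 5.47 = 82.27. Var(post) = (0.16 + 0.24) / 82.27 = 0.00486, SE 0.0697. Power = Phi(0.2 / 0.0697 - 1.96) = 82%. The pooled version gives 80.5%.

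**3. The planned interaction.**
- Var(baseline) = (0.16 + 0.16) / 82.27 = 0.00389.
- Correlation of a group's two means: r = (150 x 0.03 / 5.47) x CAC = 0.823 x CAC.
- Covariance = r x [0.16 + sqrt(0.16 x 0.24)] / 82.27 = 0.00433 r.
- Var(interaction) = 0.00486 + 0.00389 - 2 x 0.00433 r = 0.00875 - 0.00865 r.

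The last column uses a noncentral t with 4 df (six groups less two arm means; critical value 2.776).

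| CAC | r | SE | 0.2/SE | Power, normal | Power, 4 df |
|---|---|---|---|---|---|
| 0 | 0 | 0.0936 | 2.14 | 57% | 37% |
| 0.2 | 0.165 | 0.0856 | 2.34 | 65% | 43% |
| 0.4 | 0.329 | 0.0768 | 2.60 | 74% | 51% |
| 0.5 | 0.411 | 0.0721 | 2.78 | 79% | 56% |
| 0.8 | 0.658 | 0.0553 | 3.62 | 95% | 77% |
| 1.0 | 0.823 | 0.0404 | 4.95 | >99% | 95% |

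**4. Thresholds.** The interaction reaches 80% at a CAC of about 0.51 by normal approximation and about 0.83 with 4 df. It matches the single-time comparison when 2 x 0.00433 r = 0.00389, so r = 0.449 and CAC = 0.449 / 0.823 = 0.55. With equal variances the break-even is r = 0.50, CAC 0.61. Bringing in the GDP-level ICC of 0.29 (10 GDPs x 15 patients) gives 0.49 to 0.54. Depending on the definition, break-even lies between about 0.45 and 0.61.

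**5. Would a baseline-adjusted analysis always do better?** Simulating six group means with equal variances (100,000 runs) compares a group-level adjusted analysis with an estimated slope (3 df) against the interaction (4 df):

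| CAC | Variance, adjusted vs interaction | Power, adjusted vs interaction |
|---|---|---|
| 0 | 0.0073 vs 0.0097 | 42% vs 35% |
| 0.55 | 0.0058 vs 0.0053 | 50% vs 55% |
| 1.0 | 0.0024 vs 0.0017 | 81% vs 94% |

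A common-baseline estimator that pools variances does better than the estimated slope. It beats the interaction up to a correlation of about 0.85, and at 1.0 its variance is about 13% larger.

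**The case against.** The strongest case for the plan is that no shortfall is demonstrated. The same GDPs in the same groups are measured some months apart, and the Sample size section expects strong clustering within GDPs, so a high over-time correlation is plausible. At 0.8 the normal-approximation power is 95%. A model with only time-constant random intercepts would imply a correlation of 1. For the third-molar outcome the look-back is five years; if it applies at both measurements the windows overlap and the different-patients assumption fails. The interaction is also a valid, unbiased estimator, and the Discussion already concedes that the trial may be underpowered.

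Much of this stands. The loss is conditional, and the issue is power, not validity. But plausible stability is not a stated assumption, and choosing a random-effects structure does not make the true correlation 1. The doubts in the Discussion concern the effect size and the ICC, not the mismatch between calculation and test.

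A reader might go further and infer that the interaction always wastes precision, so that a model with one common baseline mean should replace it. The documents do not support that. The claim needs a known correlation or many groups, and with six groups the ranking changes with the unknown correlation (step 5). The premise of equal expected baselines is not secure either, since the Economic evaluation section lets some pre-test data be gathered during the intervention period. If any were sampled after allocation, forcing a common baseline could bias the effect.

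**Conclusion.** The concern holds as a mismatch between the power statement and the planned test. The 80% belongs to a single-time comparison. For the interaction, power runs from 57% to above 99% by normal approximation, and from about 37% to 95% with 4 df, as the group autocorrelation goes from 0 to 1. These figures rest on ICC 0.03, 150 registrations per group per period, three groups per arm and different patients in each period.

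Two limits apply. The protocol gives no autocorrelation, so it cannot be said that the trial misses 80%, only that 80% has not been shown. And part of the drop in the 4 df figures is a separate consequence of having six groups: on 4 df even the single-time comparison has about 58% power.

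**What to change.** In the Sample size section, restate the power for the allocation-by-time interaction. Give the assumed over-time correlation of group effects, show power over a range of values, say whether the same or different patients are expected in the two periods, and use degrees of freedom suited to six groups. This costs one recalculation and a few sentences; no data collection changes.

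Optionally, add a sensitivity analysis with period and period-by-allocation terms and no allocation main effect. Limit it to outcomes whose baseline data are truly complete before allocation, and reconcile the Data collection and Economic evaluation sections on that timing first. Describe it as a supporting analysis, since its precision advantage does not hold at very high over-time correlation.
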